## Abstract

**Background:**

Epidemic viral diseases have become more prevalent.. Among the various strategies to prevent such epidemics, vaccination is the most cost-effective. However, populations that are immunized are typically already exposed to multiple previous vaccinations or natural infections. Studies from this and other laboratories have revealed that pre-existing dengue antibodies can either inhibit or enhance subsequent dengue infection depending on the pre-existing antibody levels. While cross-reactive antibody is potentially pathogenic in dengue, how it impacts immune response to vaccination is unclear. Aggregated at the site of vaccination and the respective draining lymph nodes are antigen-presenting and immune regulatory cells that express Fc receptors and play pivotal roles in determining the magnitude and polarity of the immune response. Vaccine uptake by these antigen-presenting cells may thus be either inhibited or enhanced when vaccines are opsonized with cross-reactive antibodies.

**Design:**

In view of the limited knowledge on how cross-reactive antibodies affect vaccination outcome, we propose a study that exploits the known cross reactivity between Japanese encephalitis (JE) virus antibody and yellow fever (YF) vaccine. We hypothesize that cross-reactive antibodies impact antibody response to YF at the point vaccination in a concentration-dependent manner by altering both vaccine uptake and the innate immune response by antigen presenting cells. We will structure an open-label clinical trial on sequential vaccination with JE and YF vaccines, with different time intervals between vaccinations. This would test immune response to YF vaccination in subjects with different titer of cross-reactive JE vaccine-derived antibodies. The clinical materials obtained in the trial will drive basic laboratory investigations directed at elucidating how heterologous antibody affect vaccination at the molecular level. YF neutralizing antibody titer will be measured using plaque reduction neutralization test against the vaccine strain YF17D. Innate immune response will be characterized genetically using either microarray or digital PCR (or both). The innate immune response will also be characterized at the protein and metabolite level using Luminex bead technology and lipidomic/metabolomic approaches.

**Discussion:**

This proposed study represents one of the first to examine the role of cross-reactive antibodies in modulating immune responses to vaccines, the findings of which may re-shape vaccination strategy.

**Trial registration:**

Clinical Trials.gov registration number: NCT01943305 (3 September 2013).

## Background

The increasing prevalence of viral epidemics in recent decades threatens both human health and global economies. Among the countermeasures, vaccination remains the single most cost-effective method of disease prevention. One of the most popular forms of vaccines is the live attenuated vaccine (LAV). LAV is a weakened virus that is able to mimic natural infection and present antigens in native conformation to immune cells, often resulting in superior protection compared to other forms of vaccines. However, populations that are immunized are typically already exposed to multiple previous vaccinations or natural infections against a range of viruses. Since some of these viruses are evolutionarily related and share antigenic epitopes with the LAV, there is high likelihood of cross-reactivity between LAV and pre-existing antibodies evoked against previous vaccination or infection. Although the impact of these cross-reacting antibodies has largely been overlooked, there is growing evidence that its impact can be highly significant but widely varied [1-3]. Thus, cross-reactive antibodies could, in some cases, boost the efficacy of vaccines while in others render them ineffective.

Studies from this and other laboratories have revealed that pre-existing antibodies against certain dengue virus (DENV) serotypes can enhance subsequent infection with a heterologous serotype by promoting viral entry and infection into Fc receptor-expressing cells [4-7]. While the presence of cross-reactive antibodies is potentially detrimental in dengue [5,8-11], it is unclear how cross-reactive antibodies may impact the efficacy of LAV or other viral vector-based vaccines. Some of the critical sites in the body where cross-reactive antibodies could impact vaccination efficacy are at the site of vaccination [12,13] and in the secondary lymph node draining the vaccination site, where the innate and adaptive immune responses are initiated, respectively [14,15]. Aggregated at these sites are dendritic cells, monocytes, macrophages, and mast cells, which are either antigen presenting or immune regulatory cells that play pivotal roles in determining the magnitude and polarity of the immune response. As all of these cell types express Fc receptor, cross-reactive antibodies can potentially and markedly alter the nature of the initial interactions of vaccine antigens with these immune surveillance and regulatory cells and, by extension, the resulting immune response [16]. It is conceivable that cross-reactive antibodies may directly bind vaccine antigen and enhance Fc receptor uptake by antigen presenting cells resulting in an enhanced and beneficial immune response. Alternatively, these antibodies may aggregate vaccines to co-ligate inhibitory Fc receptors, a mechanism that we recently demonstrated [17], that reduces both entry into these cells and hence vaccination efficacy. This capacity of pre-existing antibodies to interfere with efficacy of vaccines may explain why the use of adenovirus and reovirus to deliver antigens has encountered very mixed results [2,3,18-21].

### Objectives and hypotheses

In view of the limited information available on the potentially critical role heterologous antibodies have in modulating the efficacy of LAVs, we propose here a study that takes advantage of the known cross-reactivity between antibodies to Japanese encephalitis (JE) virus and yellow fever (YF) vaccine. We will structure human and animal studies that inform on whether heterologous antibody affects vaccination efficacy and how this is mediated molecularly. Our long-term goal is to maximize the cost-effectiveness of vaccination by developing a personalized approach to vaccination where the dose of vaccine is tailored to the background heterologous antibody titer of the vaccinee.

We hypothesize that cross-reactive antibodies impact antibody response to YF at the point vaccination in a concentration-dependent manner by altering both vaccine uptake and the innate immune response by antigen-presenting cells.

Primary objectives:The primary objective of this clinical study is to examine the role of cross-reactive antibodies in modulating immune responses to vaccines.Hypothesis: antibody response to YF vaccination is influenced by the heterologous antibody titer at the point of YF vaccination.Hypothesis: heterologous antibody to YF affects the magnitude of vaccine uptake through the Fc receptors and alters the quality and magnitude of the innate immune response following YF vaccination, which has been previously shown to be predictive of the immune response to YF vaccination.Hypothesis: heterologous antibody titer affects the response of Fc receptor-expressing antigen presenting or immune regulatory cells to YF vaccination.

Secondary objectives:To determine neutralizing antibody response to YF vaccination in human volunteers at different time intervals following a prior JE vaccination.To characterize the innate immune response to YF vaccination at different time intervals after a prior JE vaccination.To elucidate the dendritic cell, mast cell, monocyte and macrophage response to YF vaccination in the presence of heterologous JE antibodies in humans.

Exploratory objectives:To examine how heterologous antibody titer influences the antibody response to vaccination. While an obvious approach is to enroll participants with varying titers of pre-existing antibodies, such as dengue antibodies, that cross-react with YF vaccine this would require a large population size to account for qualitative and quantitative differences. To overcome this we will take advantage of the natural reduction in cross-reactive antibodies with increasing amount of time from a prior JE vaccination.To maximize the cost-effectiveness of vaccination by developing a personalized approach to vaccination where the dose of vaccine is tailored to the background heterologous antibody titer of the vaccine.

## Methods/design

### Trial approval and conduct

The trial is approved by the Singhealth centralised Institutional Review Board (ID: 2013/385/E) and is registered on the clinicaltrials.gov registration number: NCT01943305. The trial sponsor is the Singapore General Hospital, Singapore, in collaboration with Duke-NUS Graduate Medical School, Singapore. The trial is funded by the Biomedical Research Council, Singapore (BMRC reference 13/1/96/19/689) and will be carried out in accordance with the principles of the Singapore Good Clinical Practice guidelines and in compliance with the Helsinki Declaration. Informed consent is obtained for all patients before enrolment.

### Study design

The study design is shown in Table 1. Healthy volunteers meeting all inclusion criteria will be enrolled and recruited into the study at the Singhealth Investigational Medicine Unit (IMU).

**Table 1 Tab1:** **Study design**

**Groups**	**Vaccination schedule**		
	**1st vaccination (month 1)**	**2nd vaccination (month 2)**	**3rd vaccination**
Group 1	JE vaccination	JE vaccination	Yellow fever vaccination 1 month after second JE vaccine
Group 2	JE vaccination	JE vaccination	Yellow fever vaccination 4 months after second JE vaccine
Group 3	JE vaccination	JE vaccination	Yellow fever vaccination 9 months after second JE vaccine
Group 4	Yellow fever vaccination	No vaccination	No vaccination

JE, Japanese encephalitis.

A total of 100 healthy adults, pre-screened to be negative for anti-dengue antibodies, will be enrolled upon written informed consent; 75 subjects in the test arm will receive two doses of inactivated JE vaccine (Ixiaro, Novartis (Singapore) Pte Ltd, Pharmaceutical Division [name]), while 25 subjects in the control arm will receive no JE vaccination.

Subjects in the test arm will be sub-divided into three groups who receive YF17D (Stamaril, SANOFI PASTEUR SA [name]): group 1, YF vaccination 1 month post-JE vaccination; group 2, YF vaccination 4 months post-JE vaccination; group 3, YF vaccination 9 months post-JE vaccination. Subjects in the control arm (group 4) will receive YF vaccination at month 1.

Blood sampling in relation to YF17D vaccination will take place: 1) pre-dose; 2) 1 day post-dose; 3) 3 days post-dose (+1 day); 4) 1 week post-dose (±2 days); 5) 1 month post-dose (±5 days); and 6) 6 months post-dose (±14 days).

### Selection and withdrawal of patients

#### Inclusion criteria

Healthy male or female adults, 21 to 50 years of age at the time of screening.Negative for anti-dengue antibodies by enzyme-linked immunosorbent assay (ELISA).Subjects who are willing to comply with the requirements of the study protocol and scheduled visits (for example, completion of the subject diary, return for follow-up visits) and who are willing to make themselves available for the duration of the study with access to a consistent means of telephone contact, which may be either at home or at the workplace, and be either a land line, or mobile, but not a pay phone or other multiple-user device (that is, a common-use phone serving multiple rooms or apartments).Subjects who give written informed consent approved by the Ethical Review Board governing the site.Satisfactory baseline medical assessment as assessed by physical examination and a stable health status. The laboratory values must be within the normal range of the assessing site or show abnormalities that are deemed not clinically significant as judged by the investigator. A stable health status is defined as the absence of a health event satisfying the definition of a serious adverse event.Accessible vein in the forearm for blood collection.Females of non-child bearing potential due to surgical sterilization (hysterectomy or bilateral oophorectomy or tubal ligation) or menopause.Female subjects of childbearing potential may be enrolled in the studyif they have a negative urine pregnancy test on the day of screening and negative urine dipstick pregnancy tests at the days of the vaccinationsif they use adequate, reliable contraception or abstain from sexual intercourse during the entire study for 1 year.

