#### Visit 2 – dose 1 (Japanese encephalitis)

Pre-dose vital signsUrine pregnancy test if applicableJE vaccination1 hour post-dose physical examination1 hour post-dose vital signs

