#### Visit 3 – dose 2 (Japanese encephalitis)

This visit will occur 1 month after the first JE vaccination.Pre-dose vital signsJE vaccination1 hour post-dose physical examination1 hour post-dose vital signs

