#### Visit 4 – dose 3 (yellow fever)

This visit will occur 1 month after the second JE vaccination for subjects randomized to group 1, 4 months after the second JE vaccination for subjects randomized to group 2, or 9 months after the second JE vaccination for subjects randomized to group 3.Pre-dose vital signsPre-dose research blood for YF antibody immune response and RNAYF vaccination1 hour post-dose vital signs1 hour post-dose physical examination

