#### Visit 2 – Dose 1 (yellow fever)

Pre-dose vital signsUrine pregnancy test if applicablePre-dose research blood for YF antibody immune response and RNAYF vaccination1 hour post-dose vital signs1 hour post-dose physical examination

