**Table 2 Tab2:** **Study schema for study arms 1, 2 and 3**

	**Visit 1 screening (-21 to -1 days)**	**Visit 2 - first vaccination (day 0)**		**Visit 3 - second vaccination (+2 weeks from first vaccination)***		**Visit 4 - third vaccination (+2 weeks from second vaccination)***	
		**Pre-vaccination**	**1 hour post-vaccination**	**Pre-vaccination**	**1 hour post-vaccination**	**Pre-vaccination**	**1 hour post-vaccination**
Inform consent	×						
Medical history and demographics	×						
Physical examination	×	x	x	x	x		×
Vital signs^a^	×	×	×	×	×	×	×
Hematology labs^b^	×						
Chemistry labs (liver, renal panel^c^)	×						
Dengue immunoglobulinG^d^	×						
Urine pregnancy test^e^	×	×					
Adverse events^f^	×	×		×		×	
Concomitant medications	×	×		×		×	
Blood sampling in relation to YF17D vaccination						×^g^	

*Window period: for second vaccination is +2 weeks (vaccination cannot be done earlier); for third vaccination (group 1, 2, 3) is +2 weeks (vaccination cannot be done earlier). ^a^Vital signs include temperature (oral and tympanic allowed), blood pressure, pulse rate, and respiratory rate. ^b^Hematology labs include hemoglobin, red blood cell, white blood cell, hematocrit, platelet count, neutrophil, lymphocyte, monocyte, eosinophil, basophil. ^c^Liver panel includes total protein, albumin, total bilirubin, alkaline phosphatase, ALT alanine transaminase, AST aspartate transaminase, gamma-glutamyl transpeptidase. Renal panel includes urea, sodium, potassium, chloride, bicarbonate, creatinine. ^d^Dengue immunoglobulin G will be tested by enzyme-linked immunosorbent assay. ^e^For females only. ^f^Clinical Trial Certificate Adverse Events version 4.0 will be used for grading. ^g^For third vaccination, pre-dose blood sample can be taken any time before dosing. YF, yellow fever.

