**Table 3 Tab3:** **Blood sampling schedule for study arms 1, 2, 3**

	**Visit 4**		**Visit 5 - 1 day after**	**Visit 6 - 3 days after (+1 day)**	**Visit 7 - 1 week after (±2 days)**	**Visit 8 - 15 days after (+2 days)**	**Visit 9 - 1 month after (±5 days)**	**Visit 10 - 6 months after (±14 days)**
	**Pre-vaccination (any time before dosing)**	**Post-vaccination (1 hour)**						
Physical examination		×	×	×	×	x	×	×
Vital signs^a^	×	×	×	×	×	x	×	×
Assessment for clinical symptoms (local and general symptoms)		×	×	×	×	x		
Blood sampling in relation to YF17D vaccination	×		×	×	×		×	×
Adverse events^b^	×		×	×	×	x	×	×
Concomitant medications	×		×	×	×	x	×	×

^a^Vital signs include temperature (oral and tympanic allowed), blood pressure, pulse rate, and respiratory rate. ^b^Clinical Trial Certificate Adverse Events version 4.0 will be used for grading. YF, yellow fever.

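### Women in groups 1 to 3 have no pregnancy test scheduled before JE dose 2 or the live YF dose, although the inclusion criteria require one on every vaccination day

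*Protocol article*

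**What the plan says.** **The rule.** The Inclusion criteria admit women of childbearing potential on condition of "a negative urine pregnancy test on the day of screening and negative urine dipstick pregnancy tests at the days of the" vaccinations. Tests and days are both plural. The same criterion also asks for reliable contraception or abstinence, and the Exclusion criteria rule out pregnant women.

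**The visit lists for groups 1 to 3.**
- Visit 2, JE dose 1, includes the test: "Pre-dose vital signsUrine pregnancy test if applicableJE vaccination1 hour post-dose physical examination1 hour post-dose vital signs".
- Visit 3, JE dose 2, does not: "Pre-dose vital signsJE vaccination1 hour post-dose physical examination1 hour post-dose vital signs".
- Visit 4, the YF dose, does not: "Pre-dose vital signsPre-dose research blood for YF antibody immune response and RNAYF vaccination1 hour post-dose vital signs1 hour post-dose physical examination".

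**The tables for groups 1 to 3.** In Table 2 the pregnancy-test row has two crosses, at screening and before the first vaccination. The cells for Visits 3 and 4 are empty.

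**Group 4.** Its YF visit does include the test: "Pre-dose vital signsUrine pregnancy test if applicablePre-dose research blood for YF antibody immune response". Table 5 marks it before that dose.

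**The concern.** The eligibility rule and the schedule meant to carry it out disagree. The rule attaches a negative test to each vaccination day; the schedule provides one for the first vaccination only. Staff who work from the visit lists and Table 2 would vaccinate women in groups 1 to 3 at Visits 3 and 4 without the test.

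The two omissions differ in weight. The JE vaccine is inactivated and its second dose comes about one month after a scheduled test. The YF vaccine is the live one: the Background and the Objectives treat it as a live attenuated vaccine. By the YF dose the last scheduled test is months old, and it is oldest in group 3, which waits longest.

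What is at stake is subject safety and compliance with the trial's own eligibility rule.

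**Working it through.** The protocol states no figure on this point, so there is none to reproduce. The check compares required with scheduled tests, then works out the age of the last scheduled test at the YF dose.

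**Step 1: tests required and scheduled, per woman of childbearing potential**

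| Occasion | Required by Inclusion criteria | Groups 1 to 3: visit list | Groups 1 to 3: Table 2 | Group 4: visit list and Table 5 |
|---|---|---|---|---|
| Screening | yes | yes | marked | yes |
| JE dose 1 (Visit 2) | yes | yes | marked | not given |
| JE dose 2 (Visit 3) | yes | no | empty | not given |
| YF dose (Visit 4; Visit 2 in group 4) | yes | no | empty | yes |

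Groups 1 to 3 need 4 tests and have 2 scheduled, so 2 of 3 vaccination days lack one. Group 4 needs 2 and has 2, so 0 of 1 vaccination days lacks one.

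**Step 2: could the empty cells be a reading error?** In Table 2, vital signs, adverse events and concomitant medications are all marked in the pre-vaccination columns of Visits 3 and 4. Those columns are intact, so the blanks in the pregnancy-test row are real. The visit lists leave out the test at the same two visits.

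**Step 3: age of the last scheduled test at the YF dose**

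Inputs:
- Last scheduled test: day of JE dose 1, taken as day 0 (Visit 2 list, Table 2).
- JE dose 1 to JE dose 2: 1 month (Visit 3).
- JE dose 2 to YF: 1, 4 or 9 months (Visit 4, Table 1).
- Windows: the Table 2 footnote allows +2 weeks for the second vaccination, and "for third vaccination (group 1, 2, 3) is +2 weeks (vaccination cannot be done earlier"). I read these as delays added to the nominal intervals, so together they add at most 14 + 14 = 28 days.
- Month length: 30.44 days, an assumption.

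Formula: nominal age = (1 + interval from JE dose 2 to YF) × 30.44 days; latest age = nominal + 28 days.

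| Group | n | Nominal | Latest |
|---|---|---|---|
| 1 | 25 | (1 + 1) × 30.44 = 61 days | 61 + 28 = 89 days |
| 2 | 22 | (1 + 4) × 30.44 = 152 days | 152 + 28 = 180 days |
| 3 | 28 | (1 + 9) × 30.44 = 304 days | 304 + 28 = 332 days |
| 4 | 25 | same visit | same visit |

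**Step 4: how many people.** The three JE groups hold 25 + 22 + 28 = 75 of 100 subjects. No sex split is given, so 75 is an upper limit.

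**Step 5: a minor point in the same criterion.** The contraception clause asks for cover over the whole study and also for one year. In group 3 these differ: JE dose 1 to the 6-month post-YF visit is nominally 1 + 9 + 6 = 16 months. (Table 4 shows a last visit one year after YF, which would make it 1 + 9 + 12 = 22 months; I follow the visit lists and Table 3.) If the year starts at JE dose 1, which the protocol does not say, it still covers the YF dose and 365 − 304 = 61 days after it, or 365 − 332 = 33 days with both windows used in full. No safety consequence is shown.

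**The case against.** The strongest reply is that the safeguard already exists. The inclusion criterion states it without exception and nothing in the protocol waives it at Visits 3 or 4. Pregnancy is an exclusion, contraception or abstinence is required, and the Principal Investigator may stop participation that could be harmful. The visit lists are also not exhaustive: those for Visits 2 to 4 omit the adverse-event and concomitant-medication checks that Table 2 marks, so absence from a list is weak evidence that a procedure is not planned. The article condenses a fuller protocol that is not shown, and Figure 1 could not be checked.

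Part of this stands. What staff would do is conditional on their following the printed schedule. The lists alone would not settle the matter. Table 3 adds little, since it is titled "Blood sampling schedule for study arms 1, 2, 3" and has no eligibility rows. The contrast with group 4 also need not reflect a decision to check one arm and spare three: both schemas place the test at screening and at the first vaccination, and group 4's first vaccination happens to be YF.

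It does not remove the contradiction. Table 2 carries the pregnancy-test row and leaves the same two visits empty, in agreement with the lists. The article does not leave the test to a fuller document: it prints the schedule and names the test where it is planned. Contraception and the exclusion lower the risk, but the criterion asks for the same-day test in addition. A condition placed among the inclusion criteria for a dose nominally up to 10 months after the first vaccination is easily missed unless the visit schedule repeats it.

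**Conclusion.** The concern holds. For groups 1 to 3 the schedule omits the required test on 2 of 3 vaccination days, including the day of the live vaccine, whereas group 4 has its test that day. At the YF dose the last scheduled test is 61 to 89 days old in group 1, 152 to 180 in group 2 and 304 to 332 in group 3.

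These ranges assume a 30.44-day month and run from no delay to full use of both windows. The number of women exposed is unknown, with 75 as the ceiling. The omission before YF is the serious part; the one before JE dose 2 matters less, and the contraception wording is minor. The error should be corrected on safety and eligibility grounds; no effect on the antibody comparison, power or type 1 error is claimed.

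**What to change.** 1. Add a urine pregnancy test, where applicable, before dosing in the Visit 3 and Visit 4 lists for groups 1 to 3.
2. Mark the pre-vaccination cells of Visits 3 and 4 in the pregnancy-test row of Table 2.
3. Give the dose only after a negative result, as the inclusion criterion already implies. All four groups then have the same check on the YF day.
4. Minor: remove the one-year limit from the contraception clause, or state the duration by group.

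The cost is one line in each of two lists, two table cells and one deleted phrase. The dipstick test is already required, so no new procedure is introduced. The Trial status section says recruitment was still open, so the correction could still protect participants.
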